### Sample size

The sample size of 205 PDAC cases was based on a target sensitivity of 85%, with 7% precision and 80% power, informed by pilot data on 132 patients.^10^ We aim to recruit the same number of each type of control, totalling 615 participants with complete data. Allowing for 20% attrition due to loss of samples, we will recruit 771 participants, which includes at least 256 with cancer.

Riley *et al*^11^ also recommend ensuring that the sample size achieves small mean absolute prediction error (MAPE), defined as the mean absolute difference between predicted and observed outcomes (cancer=1, no cancer=0), and large variation explained by the CPM, measured by Cox-Snell R^2^, which ranges from 0 for no predictive value to 1 for perfect prediction. Additionally, the area under the receiver-operating curve (AUC) provides an estimate of the ability of the CPM to discriminate between cancer and non-cancer cases. The resulting CPM based on 615 participants will have an MAPE of 0.048, estimate cancer incidence with precision 0.088, and achieve a minimum Cox-Snell R^2^ of 0.431 based on forty predictors. The SE in the AUC achieved by the CPM will be 0.016, based on an AUC of 0.86.

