#### Developing and reporting the CPM

Initially, relationships between candidate VOCs and the presence of PDAC will be explored using univariate logistic regression models, including linear, polynomial and cubic splines.

Given the large number of initial variables, a screening step will be undertaken to identify the most promising candidate VOCs for inclusion in statistical models, with approximately the top 50 being retained. To develop the CPM, a logistic regression model with variable selection and importance assessment techniques will be fitted. Robust variable selection methods will be used, specifically the least absolute shrinkage and selection operator (LASSO) and elastic net. LASSO aids in selecting a more parsimonious model by shrinking less important predictor coefficients to zero, while elastic net combines the penalties of LASSO and Ridge regression, effectively managing correlated predictors.^14^

Elastic net is particularly beneficial when dealing with highly correlated variables, as it can select groups of related predictors, making it well-suited for multivariate datasets like VOC profiles. The best-performing model, determined through nested cross-validation (CV), will be advanced for further analysis.

In addition to the statistical methods, random forest and deep neural networks (DNNs) will be used to enhance model predictions. Random forest constructs multiple decision trees from different data subsets and combines their predictions, handling complex, non-linear relationships in the VOC data and identifying key VOCs that predict PDAC. DNNs, capable of capturing patterns in high-dimensional data, will be employed to model non-linear relationships in the VOC data. The DNN architecture will include a designed number of hidden layers and neurons, with regularisation techniques like dropout applied to prevent overfitting.

The model will be enhanced by assessing the additional diagnostic value of patient and clinical features (eg, family history of cancer, presenting symptoms), potentially improving its predictive power and clinical applicability.

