A 10-fold CV will be used for internal validation of statistical and machine learning models. Nested CV will be applied to best identify the penalty terms in LASSO and elastic net models, as well as to fine-tune the hyperparameters in random forest and DNNs, reducing the risk of overfitting across all models. For each fold in the internal CV, the sensitivity, AUC, precision-recall AUC and the MAPE will be calculated and summarised by median (IQR) values across folds. Apparent performance with 95% CIs and optimism will be calculated by 100 bootstrap resamples. Predictors chosen in ≥50% bootstrapped selection routines will be taken forward.

For the final model, bias-corrected ROC (receiver operating characteristic) curves and calibration plots will be provided. All model coefficients with SEs, and ORs with 95% CIs will be reported.

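### 100 bootstrap resamples are too few for 95% percentile limits and, apparently, for the predictor vote; if the interval comes from refitted models it is also shifted above the apparent AUC

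*Protocol article*

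**What the plan says.** All of this is in the protocol article, under Developing and reporting the CPM, unless noted.

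- Bootstrap: "Apparent performance with 95% CIs and optimism will be calculated by 100 bootstrap resamples". One count serves the interval and the optimism. The type of interval is not named, nor is it said whether the model is refitted or held fixed when the interval is calculated.
- Selection: "Predictors chosen in ≥50% bootstrapped selection routines will be taken forward". No separate count is given, so the 100 resamples apparently apply here too. This sentence also shows that selection is rerun in the resamples.
- Screening: candidate VOCs are cut down before modelling, "with approximately the top 50 being retained". The number before screening is not given.
- Other performance reporting: "A 10-fold CV will be used for internal validation of statistical and machine learning models", summarised by medians and interquartile ranges over the folds. For the final model, "bias-corrected ROC (receiver operating characteristic) curves and calibration plots will be provided".

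The interval from the 100 resamples is the only 95% CI that the article states for model performance.

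**The concern.** There are two separate issues.

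**Count.** An average, such as the optimism, is reasonably stable with 100 resamples. A 2.5th or 97.5th percentile is not: only 2.5 of 100 values lie beyond each limit. A vote with a hard cut at 50% is also sensitive. A predictor whose long-run selection rate is close to the cut enters or leaves the model by the luck of the random seed.

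**Source of the interval.** Estimating optimism requires refitting the model in every resample. A refitted model overfits a resample that already carries the noise of the study sample, so its apparent AUC tends to exceed that of the study's own model. Percentile limits of those refitted values would describe something higher than the apparent AUC they are attached to. At stake is the position of the one stated 95% interval, and the reproducibility of the final predictor set.

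**Working it through.** **1. Inputs, and the article's own figure.** Under Sample size: "The sample size of 205 PDAC cases was based on a target sensitivity of 85%, with 7% precision and 80% power" and "We aim to recruit the same number of each type of control, totalling 615 participants with complete data", hence 205 cases and 2 × 205 = 410 controls. The same section says "The SE in the AUC achieved by the CPM will be 0.016, based on an AUC of 0.86".

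Newcombe's formula with A = 0.86, n = 615 and case fraction p = 1/3 is

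var = A(1−A)[1 + (n/2−1)(1−A)/(2−A) + (n/2−1)A/(1+A)] / [n²p(1−p)]

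= 0.1204 × [1 + 306.5 × (0.1228 + 0.4624)] / 84,050 = 0.000258, so SE = 0.0161.

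This reproduces 0.016. The article gives no figure for the bootstrap interval itself.

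**2. Monte Carlo error of a percentile limit** (near-normal bootstrap distribution assumed). SE = √(0.025 × 0.975 / B) / φ(1.96), in bootstrap SDs, with φ(1.96) = 0.0584.

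- B = 100: 0.01561 / 0.0584 = 0.27 SD.
- B = 2,000: 0.00349 / 0.0584 = 0.06 SD.

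The half-width of a 95% interval is 1.96 SD. At B = 100 the SE is therefore 0.27 / 1.96 = 14% of the half-width, and the 95% margin is 1.96 × 14% = 27%. With an SD of 0.016, the SE of a limit is about 0.27 × 0.016 = 0.004 AUC, against 0.06 × 0.016 = 0.001.

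**3. Selection vote.** Near the 50% cut the SE is √(0.5 × 0.5 / B): 0.050 for B = 100 and 0.011 for B = 2,000.

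**4. Position of the interval if it is taken from refits.** Simulation: 205 cases, 410 controls, independent normal predictors of which 10 are informative, attainable AUC 0.88, 100 resamples with the model (and the screen, where used) refitted each time. There were 120 datasets per row without screening and 80 with. LASSO penalties were fixed, not tuned (C is the inverse penalty). The 300 candidates before screening are an assumption.

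| Scenario | Apparent AUC | Mean refitted apparent AUC | Shift | Estimated optimism | Shift / optimism | Refit interval | Misses apparent AUC |
|---|---|---|---|---|---|---|---|
| 40 predictors, unpenalised | 0.899 | 0.918 | 0.019 | 0.038 | 0.5 | 0.894–0.940 | 9% |
| 50 predictors, LASSO C = 0.1 | 0.891 | 0.911 | 0.020 | 0.028 | 0.7 | 0.887–0.932 | 17% |
| 50 predictors, LASSO C = 0.3 | 0.901 | 0.923 | 0.022 | 0.039 | 0.6 | 0.901–0.944 | 49% |
| 300 screened to 50, LASSO C = 0.1 | 0.921 | 0.952 | 0.031 | 0.053 | 0.6 | 0.936–0.966 | 100% |
| 300 screened to 50, unpenalised | 0.933 | 0.960 | 0.028 | 0.069 | 0.4 | 0.944–0.975 | 100% |

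AUCs and limits are means over datasets. Shifts were averaged before rounding.

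The shift is only part of the optimism because the estimated optimism also contains the drop when a refitted model is tested back on the study sample. In the first row that test AUC is 0.918 − 0.038 = 0.880, so the optimism of 0.038 splits into 0.019 above the apparent AUC and 0.899 − 0.880 = 0.019 below it.

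A second simulation, with attainable AUC 0.86 and 60 studies, gave similar shifts. With 40 predictors the apparent AUC was 0.884 and the interval 0.879–0.929, midpoint 0.904, shift 0.020. With 300 screened to 50 the figures were 0.920 and 0.933–0.965, midpoint 0.949, shift 0.029, and the interval contained the apparent AUC in 0 of 60 studies.

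**5. Same resamples, model held fixed.** In the first simulation the interval contained the apparent AUC in every dataset, for example 0.874–0.922 around 0.899.

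**The case against.** The strongest reply is that the article names neither percentile limits nor refitted models as the source of the interval. The same resamples could be used to re-evaluate the fixed final model, and a condensed article may leave that choice to the full analysis plan. This stands: the shift is conditional. It does not remove the count, which the article states.

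The count also matters less under another construction. Limits set at ±1.96 bootstrap SD would have a Monte Carlo SE of about 1.96 / √(2 × 99) = 0.14 SD, half the percentile figure. On the first simulated interval (half-width 0.023) the percentile SE is 0.14 × 0.023 = 0.003 AUC, which is modest.

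Three stronger readings may tempt a reader, and none is supported:

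- *The interval moves up by the whole optimism.* It moved by 0.4 to 0.7 of the estimated optimism. In the second simulation it moved by 0.020 of an apparent-minus-true gap of 0.047 (43%) and by 0.029 of 0.115 (25%).
- *Missing the true AUC proves that refitting is the error.* Refit intervals missed the true AUC in 90–100% of datasets, but fixed-model intervals missed it in 40–100%. An interval for apparent performance is not built to cover performance in new patients.
- *Readers would be left with an uncorrected figure.* The article calls the quantity apparent and also promises optimism, bias-corrected ROC curves, calibration plots and cross-validation. These limit the harm, though they do not repair the interval.

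**Conclusion.** The point holds in limited form. A count of 100 is too small for 95% percentile limits (SE about 0.27 SD each, 14% of the half-width) and for a vote that decides which predictors are kept (SE 5 points near the cut). The first figure assumes percentile limits; the second assumes that the vote uses the same 100 resamples. Neither depends on how the refits are used.

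If the interval is also taken from the refits, which is the most natural reading but is not stated, it is shifted about 0.02 to 0.03 above the apparent AUC. It may then exclude the value it is meant to describe: occasionally to about half the time without screening, and always in the simulations with screening rerun in each resample. The direction was the same in every scenario. The sizes rest on assumptions that the article does not supply: independent predictors, 10 informative VOCs, fixed penalties and 300 candidates before screening. The documents do not show that the article prescribes a refit-based interval.

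**What to change.** - Raise the count from 100 to about 2,000 resamples for any percentile limit and for the selection vote.
- Use the refitted resamples only to estimate optimism.
- Calculate the CI for apparent performance with the fitted model held fixed, by DeLong's method or by resampling participants without refitting, and say which.
- Label that interval as not covering performance in new patients.

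The cost is a few sentences in the analysis plan and computing time. Recruitment and data collection are unaffected.

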#### Outlier and missing data considerations

Since very high values of some VOCs may be indicative of PDAC, measurements considered extreme will be assessed by study clinicians/scientists without knowledge of the study group. Any excluded values will be documented and reported.

The primary analysis will use complete data. If individual VOCs are missing, we will assume ‘missing at random’ conditional on cancer status and all other predictors.^15^ If indicated by the missing data patterns, a sensitivity analysis will be conducted, imputing missing VOCs using chained equations to produce 20 datasets. Imputation models will be developed for cases and controls separately and will be consistent with the substantive logistic model. CPM development will be repeated for each imputed dataset and a final set of predictors will be identified. Using this final set, CPMs will be fitted for each imputed dataset and the results will be combined using the Rubin rules.^16^

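### In the imputed-data sensitivity analysis, imputing VOCs by diagnosis before cross-validation may inflate validated performance and hide the accuracy lost to missing VOCs

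*Protocol article*

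**What the plan says.** The protocol article, under Outlier and missing data considerations, sets the main route first: "The primary analysis will use complete data". Missing VOCs are assumed missing at random "conditional on cancer status and all other predictors". Only if the missing-data patterns indicate it, "a sensitivity analysis will be conducted, imputing missing VOCs using chained equations to produce 20 datasets". For that analysis, "Imputation models will be developed for cases and controls separately and will be consistent with the substantive logistic model". Next, "CPM development will be repeated for each imputed dataset and a final set of predictors will be identified"; models using that set are fitted in each dataset and pooled by Rubin's rules.

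Under Developing and reporting the CPM: "A 10-fold CV will be used for internal validation of statistical and machine learning models". In each fold, "the sensitivity, AUC, precision-recall AUC and the MAPE will be calculated and summarised by median (IQR) values across folds". Nested cross-validation tunes the penalties and hyperparameters. Apparent performance and optimism come from 100 bootstrap resamples, which also decide which predictors go forward.

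The article does not place imputation relative to the folds or resamples. It does not say whether performance will be reported from the imputed datasets, or how a missing VOC would be handled in a patient whose diagnosis is not yet known.

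**The concern.** Using the outcome when imputing predictors is sound for estimating coefficients, and it fits both the stated missing-at-random assumption and the logistic model. The difficulty is confined to records used for validation. The natural reading is that the 20 datasets are completed first and development, which in this article includes internal validation, is then rerun in each. A held-out case's missing VOCs would have been drawn from a model fitted only to cases, and a held-out control's from one fitted only to controls, so the test fold carries part of its own label. Bootstrapping data that are already imputed would not remove this.

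The test is meant for triage in general practice, where diagnosis is unknown and status-specific imputation cannot be run. What is at stake is the purpose of the sensitivity analysis: performance could look stable however many VOC values were missing. The same section has extreme VOC values judged blind to study group, so letting group determine the imputed values used in validation sits awkwardly beside it.

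**Working it through.** **The plan's own figure.** The basis is "The sample size of 205 PDAC cases was based on a target sensitivity of 85%, with 7% precision and 80% power". With two-sided alpha 0.05 (assumed), n = (1.960 + 0.842)² × 0.85 × 0.15 / 0.07² = 204.2, so 205. Three groups give 3 × 205 = 615. With 20% attrition, 205 / 0.8 = 256.25, so 257 per group and 3 × 257 = 771. These reproduce and are not affected by this point.

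**Simulation 1.** The protocol supplies 205 cases, 410 controls, forty predictors, 10 folds and the median AUC across folds. Assumed: pairwise correlation 0.3; values missing completely at random; ridge logistic regression; signal, where present, in 8 VOCs; 30 replicates with 2 imputations each. Chained equations were run separately in cases and controls on the whole dataset, followed by cross-validation. The comparator applies the models developed on the status-imputed data to new patients with the same missingness, imputed from their other VOCs without diagnosis.

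No true signal (the correct AUC is 0.50):

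| Missing per VOC | CV, nothing missing | CV, imputed by status | New patients, status-blind |
|---|---|---|---|
| 2% | 0.504 | 0.509 | 0.499 |
| 5% | 0.482 | 0.498 | 0.503 |
| 10% | 0.509 | 0.541 | 0.500 |
| 20% | 0.494 | 0.562 | 0.497 |
| 30% | 0.506 | 0.606 | 0.503 |

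Signal near the planned AUC of 0.86:

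| Missing per VOC | (a) CV, nothing missing | (b) CV, imputed by status | (c) New patients, complete VOCs | (d) New patients, status-blind | b − d | b − a |
|---|---|---|---|---|---|---|
| 2% | 0.852 | 0.849 | 0.851 | 0.848 | 0.001 | −0.003 |
| 5% | 0.853 | 0.854 | 0.853 | 0.847 | 0.007 | 0.001 |
| 10% | 0.852 | 0.857 | 0.846 | 0.833 | 0.024 | 0.005 |
| 20% | 0.849 | 0.854 | 0.844 | 0.816 | 0.038 | 0.005 |
| 30% | 0.855 | 0.864 | 0.830 | 0.791 | 0.073 | 0.009 |

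Standard errors are 0.003–0.009 for the cross-validated columns and 0.001–0.003 for new patients. Column b stays flat while column d falls from 0.848 to 0.791. For new patients with complete VOCs the overstatement (b − c) at 10% and 20% missing is 0.857 − 0.846 = 0.011 and 0.854 − 0.844 = 0.010.

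**Simulation 2.** Same group sizes and correlation, 50 VOCs, 30 replicates, standard error about 0.006. With no signal, the AUC under status-specific imputation was 0.51, 0.53 and 0.58 at 5%, 10% and 20% missing, against 0.49–0.51 when status was not used. With signal and a full-data AUC of 0.76, status-specific imputation gave 0.77 at 10–20% missing, against 0.73 (10%) and 0.70 (20%) without status. The gaps are 0.77 − 0.73 = 0.04 and 0.77 − 0.70 = 0.07, or up to 0.08 allowing for rounding. This comparator also left status out for training records, so it does not isolate the treatment of held-out records as Simulation 1 does.

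**Scale.** The protocol plans a standard error of 0.016 for the AUC. A gap of 0.038 is 0.038 / 0.016 = 2.4 of these; a gap of 0.007 is 0.4.

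**The case against.** The strongest reply is that little of the study depends on this step. The primary model and its cross-validation contain no imputed values. The imputed analysis is conditional, and its described end product is a predictor set with pooled coefficients, for which status-specific imputation is appropriate. Fold-level detail may sit in an analysis plan that is not shown. All of this stands, and it limits the point to performance computed from the imputed datasets.

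A reader might infer that the study's validated performance as a whole is inflated and cannot be reproduced in patients of unknown status. The documents do not support that. The main results use complete data, and a patient with all VOCs measured can be scored without imputation.

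The size is also open to challenge. With signal present, the status-imputed AUC is within about 0.01 of the full-data AUC; the larger gap appears only against patients who themselves lack VOCs. The 20% attrition is attributed to lost samples, not single VOCs. If VOCs were missing independently, 10% per VOC across forty would leave 0.90^40 = 1.5% of records complete, too few for the planned primary analysis, so 10–20% is plausible only if missingness clusters within participants. That too stands. It also cuts the other way: at 5% per VOC only 0.95^40 = 13% would be complete, and the imputed results would then carry much of the weight.

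What the reply does not remove is that the article itself fixes imputation by diagnosis and places repeated model development after it, with nothing to protect held-out records.

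**Conclusion.** The point holds as a limited one that should be corrected. Followed on its natural reading, the sensitivity analysis would validate on records whose missing VOCs were filled in using their own diagnosis. Performance may then be overstated, and the loss of accuracy from missing VOCs would be masked.

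The effect is small at about 5% missing per VOC or less (0.007 or below near the planned AUC). At 10–20% missing, the no-signal AUC is about 0.53–0.58, and with signal the excess over status-blind imputation is about 0.02–0.08: 0.02–0.04 near the planned AUC, larger in the weaker-signal simulation.

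This rests on three things the article does not state: the missingness rate, that cross-validation and bootstrap are run on already imputed data, and that performance from those data will be reported. The simulations also assume a correlation of 0.3, values missing completely at random, and ridge regression where the protocol names LASSO and elastic net. The figures are illustrative; the direction follows from the mechanism.

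**What to change.** Add to Outlier and missing data considerations that, for any performance reported from imputed data:

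- imputation models are fitted within each training fold or bootstrap sample, with the outcome allowed for training records;
- held-out records are imputed from their other predictors, by a model fitted to the training records that does not use cancer status;
- status-specific imputation of the whole dataset is kept for the final pooled coefficients only.

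State also how a missing VOC would be handled when the test is used. If no performance is to be reported from the imputed datasets, saying so removes most of the problem, although penalty tuning by cross-validation would still run on status-imputed records.

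The cost is computing. With 20 imputations, 10 folds need 20 × 10 = 200 completed datasets and 100 bootstrap samples need 20 × 100 = 2,000, before inner tuning loops, in place of 20. The reported AUC may be lower. Recruitment, sample size and the primary analysis do not change.

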#### Derivation of diagnostic rules

A clinical decision rule will be derived from probabilities of PDAC generated by the final CPM, with thresholds for referral for definitive testing, review within 6 months and discharge.

Development of decision rules will consider the cost of missing a PDAC case and of incorrectly declaring PDAC in the control group. The net benefit of the CPM will be calculated across a range of candidate thresholds.^17^ We will use decision curve analysis^18^ to compare the net benefit of the proposed CPM against the current standard of care of referring all symptomatic patients. We will also consider the threshold which maximises the expected number of patients taking the test before misdiagnosis occurs, weighted by the ‘clinical cost’ of a false negative relative to a false positive.^19^ This relative ‘clinical cost’ will be elicited from expert clinicians and members of the study steering group, which includes patient representatives.

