### Objectives

The objective of the VAPOR 1 (Volatile organic compound Assessment in Pancreatic ductal adenOcaRcinoma) study is to develop and internally validate a clinical prediction model (CPM) to triage the risk of PDAC based on profiles of VOCs obtained from the non-invasive breath test. The clinical utility of the model to enable referral for the appropriate reference test will be investigated, and the additional value of patient and clinical characteristics will be assessed. This will then be compared against the current standard practice for all patients presenting with symptoms indicative of pancreatic cancer.

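### The referral thresholds, net benefit and decision curve are tied to the final model's own probabilities, and no planned optimism correction is extended to them

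*Protocol article*

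**What the plan says.** The aim in the Objectives is to "develop and internally validate a clinical prediction model (CPM) to triage the risk of PDAC"; no external data set is planned.

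Under Developing and reporting the CPM, the article plans 10-fold cross-validation: "For each fold in the internal CV, the sensitivity, AUC, precision-recall AUC and the MAPE will be calculated". No cut-off is given for that sensitivity. It then adds: "Apparent performance with 95% CIs and optimism will be calculated by 100 bootstrap resamples". For the model finally chosen it states: "For the final model, bias-corrected ROC (receiver operating characteristic) curves and calibration plots will be provided".

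Under Derivation of diagnostic rules: "A clinical decision rule will be derived from probabilities of PDAC generated by the final CPM", with thresholds for three actions (refer, review, discharge). The criterion is cost-based: "Development of decision rules will consider the cost of missing a PDAC case and of incorrectly declaring PDAC in the control group". Clinical utility is then assessed: "The net benefit of the CPM will be calculated across a range of candidate thresholds", and a decision curve compares the model with referring all symptomatic patients.

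The figure of 85% appears only under Sample size: "target sensitivity of 85%, with 7% precision and 80% power".

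**The concern.** The final CPM is a single fitted model, and the only people for whom the study can generate its probabilities are those used to fit it. Fitted probabilities are too extreme: cases score higher and controls lower than new patients would. A threshold chosen and judged on them looks better than it is, in sensitivity, in specificity and in net benefit.

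The article plans two forms of validation, and neither is connected to the rule. The cross-validated sensitivity has no stated cut-off, and sensitivity depends heavily on the cut-off. The bias correction promised for the final model names ROC curves and calibration plots. A corrected ROC curve does not by itself correct a probability threshold picked on over-extreme values, nor a decision curve drawn from them.

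The decision curve answers the clinical-utility part of the study's objective. Optimism in it understates missed PDAC and overstates the gain over referring everyone. This is separate from the artificial case fraction of one third: it arises even within the study's own case mix.

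**Working it through.** **1. The plan's own figures.** From Sample size: sensitivity 0.85, precision 0.07, power 80%; two-sided 5% is assumed because alpha is not stated.
- Cases: n = 0.85 × 0.15 × (1.960 + 0.842)² / 0.07² = 0.1275 × 7.849 / 0.0049 = 204.2, so 205.
- Total: 3 × 205 = 615. With 20% attrition, 205 / 0.8 = 256.25, so 257 per group and 771 in all.
- Forty predictors, Cox-Snell R² 0.431, shrinkage 0.9 (assumed): n = 40 / [(0.9 − 1) × ln(1 − 0.431/0.9)] = 40 / 0.0652 = 614.

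All agree with the article. So N = 615, 205 cases, 40 predictors and AUC 0.86 are fair inputs.

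**2. How far sensitivity depends on the cut-off.** Equal-variance binormal scores: d′ = √2 × Φ⁻¹(0.86) = 1.528. With case fraction 1/3, the score cut-off at probability p is c = ln[2p/(1 − p)]/d′ + d′/2, and sensitivity is Φ(d′ − c).
- p = 0.5: c = 0.454 + 0.764 = 1.218; sensitivity Φ(0.310) = 62%, specificity 89%.
- p = 1/3: c = 0.764; sensitivity and specificity both 78%.
- At sensitivity 85%, specificity is 69%.

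The same model shows 62% or 78% depending on a choice that the article does not state. These two cut-offs are examples and do not come from the protocol.

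**3. Size of the optimism.** Simulated studies of 205 cases and 410 controls, with independent normal predictors, logistic regression and true AUC 0.86. The cut-off is set where 175 of 205 cases are positive (85.4%; the nominal 85%). Sensitivity in new patients is computed exactly from the fitted coefficients. Net benefit = sensitivity × 1/3 − (1 − specificity) × 2/3 × pt/(1 − pt), with pt the probability at that cut-off. There are 60 studies per row, so with a between-study SD of about 3 points the simulation error is about 3/√60 = 0.4 points.

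| Predictors | Sensitivity in new patients, cut-off set on fitted probabilities | Bootstrap-corrected estimate of it | Sensitivity in new patients, cut-off set on out-of-fold probabilities | Net benefit, apparent | Net benefit, new patients |
|---|---|---|---|---|---|
| 10 | 83.6% | 83.7% | 85.0% | 0.216 | 0.210 |
| 20 | 82.4% | 82.4% | 85.2% | 0.219 | 0.206 |
| 40 | 79.4% | 79.8% | 85.6% | 0.221 | 0.195 |

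With 40 predictors, LASSO or elastic net gives 79.2% to 81.9%, depending on how many predictors carry signal. Setting the cut-off on out-of-fold probabilities lowers specificity from 71% to 62%, which is the real price of reaching 85%.

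The article screens down to about 50 VOCs from a number it does not give. Assuming 200 VOCs, true AUC 0.90 and screening on the full data, sensitivity in new patients is 72% to 76%; from 500 VOCs with LASSO it is about 70%.

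**4. Net benefit at a fixed threshold.** At 0.10, referring everyone has net benefit 1/3 − 2/3 × 0.1/0.9 = 0.259. With 40 predictors the model's gain over this is 0.022 apparent, 0.010 from out-of-fold probabilities, 0.011 to 0.012 after bootstrap correction, and 0.010 to 0.011 in truth.

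**The case against.** **The article is condensed.** It does not say that the probabilities are uncorrected, and an analysis plan may say otherwise. This has some force, but the article does name the source of the rule as the final model. Out-of-fold probabilities come from ten other models, so a reader who follows the text would use the fitted ones.

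**The bootstrap sentence is general.** It follows directly on a list that includes sensitivity and is not limited to ROC curves. This stands. Optimism in sensitivity may already be intended, and the method works: 79.8% corrected against 79.4% true with 40 predictors. What is missing is the link from that sentence to the thresholds and net benefit.

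**No rule is set at 85% sensitivity.** This also stands. A reader might infer that the planned test will deliver 78% to 82% in place of 85%. The documents do not support that: 85% is a sample-size input, thresholds are chosen by net benefit and elicited cost, and a three-way rule has no single sensitivity. At a threshold of 0.10, sensitivity is 95.9% apparent and 92.7% true with 40 predictors, and 95.8% and 95.1% with 10. The loss there is about 1 to 3 points.

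**Timing.** A reader might also infer that fold-wise sensitivity is computed before any threshold exists. That rests only on the order of the subsections; a default cut-off may be meant. The supportable point is that none is stated.

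**Conclusion.** The concern holds as a fault in how the rule is to be evaluated. Followed as written, the thresholds, their sensitivity and specificity, and the decision curve would rest on uncorrected probabilities, and the fold-wise sensitivity would not validate the rule.

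The size is conditional. It is small with 10 predictors (about 1 to 2 points of sensitivity). With the 40 predictors that the article assumes, it is about 6 points with plain logistic regression, comparable with the planned 7-point precision, and about half of the net-benefit gain at 0.10 disappears. It grows if many VOCs are screened on the full data. The figures assume independent normal predictors, true AUC 0.86 (0.90 in the screening runs) and the design's case fraction of one third. They show how large the optimism can be; they do not forecast the study's result.

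**What to change.** In Derivation of diagnostic rules, state that net benefit, the decision curve, and sensitivity and specificity at the chosen thresholds are computed in one of two ways:
- from out-of-fold probabilities; or
- with the bootstrap optimism correction already planned.

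In either case VOC screening, predictor selection and threshold choice are repeated within each resample. Both are valid. With heavy screening the out-of-fold route is the safer one: in the run with 200 VOCs and plain logistic regression, at the cut-off set on fitted probabilities, the bootstrap-corrected sensitivity was 74.9% and the out-of-fold estimate 71.3%, against a true 72.3%.

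In Developing and reporting the CPM, report held-out sensitivity pooled over folds, with specificity, at the thresholds of the decision rule. Each fold holds only about 205/10 ≈ 20 cases, so a single case moves a fold's sensitivity by about 5 points.

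The cost is a few sentences and extra computing, since the bootstrap selection of predictors has to be rerun inside each fold or resample. The reported sensitivity and net benefit will be less favourable. No data collection changes.
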